#### Measurement of Secondary Outcomes

Anxiety was measured with the GAD-7 as a secondary outcome. The GAD-7 is a brief, self-administered scale with a few measures for measuring anxiety that was first administered to primary care patients [32,33]. The scale has been translated into other languages. People have adjusted the items to suit different contexts. It has high psychometric qualities, which enables it to detect anxiety and depression quickly and precisely [32]. Items are rated from 0 (absence of anxiety) to 3 (anxiety is felt most of the days) [33], and the overall score ranges from 0 to 21. Higher scores indicate that the respondent exhibits more anxiety symptoms. In this study, the GAD-7 demonstrated strong reliability and validity in terms of criteria, the concept, and factorial and procedural measures. An optimal cut-off was set that maximized sensitivity (89%) and specificity (82%) [32].

To determine the psychological well-being of participants, we measured their life satisfaction, sense of self-efficacy, and self-compassion. Life satisfaction was measured with the Satisfaction With Life Scale (SLS). Perceived self-efficacy was measured with the Teachers’ Sense of Efficacy Scale (TSES) [34]. For the TSES, higher scores show a higher sense of self-efficacy. The reliability of the TSES subscales was 0.91 for instruction, 0.90 for management, and 0.87 for engagement. The intercorrelation among the instruction, management, and engagement subscales was 0.60, 0.70, and 0.58, respectively, with a significance level of *P*<.001 [34]. Self-compassion was measured with the 12-item Self-Compassion Survey—Short Form (SCS-SF) [35]. The SCS-SF includes 3 subscales: self-kindness versus self-judgment, common humanity versus isolation, and mindfulness versus overidentification. Higher scores indicate higher self-compassion. The internal consistency of the SCS-SF was found to be satisfactory, with Cronbach α of .86 or higher in all samples [35].

In addition, depression symptoms of the participants were measured using the GHQ-12. This scale has been psychometrically validated for use as a screening instrument for depression symptoms in primary health services in numerous countries and has high validity and reliability [36]. Reliability analysis revealed a respectable outcome, with Cronbach α of .87 [37]. The most common scoring methods are bimodal (0-0-1-1) and Likert scoring styles (0,1,2,3) [37]. For the GHQ-12, higher scores indicate depression and physical and social dysfunction. The perceived stress condition was assessed using the 10-item Perceived Stress Scale (PSS) [38]. This scale examines the responses of participants to a variety of potentially stressful circumstances with 2 variables. The reliability coefficients for the scores on these 2 variables were 0.87 and 0.73, respectively [38]. Higher scores indicate a higher level of perceived stress.

The mindfulness trait was assessed using the Five Facet Mindfulness Questionnaire (FFMQ). This instrument was created on the basis of a factor analytic assessment of 5 independently developed mindfulness questionnaires [39]. The FFMQ has repeatedly demonstrated strong psychometric qualities, including high levels of construct validity and reliability. The subscales of the FFMQ have Cronbach α ranging from 0.73 to 0.91, indicating good internal consistency [40]. Baer et al [39] identified 5 parameters that appear to represent mindfulness aspects as they are currently conceived: observing, describing, acting with awareness, not judging the inner experience, and not reacting to the inner experience. Higher scores indicate a greater level of mindfulness in individuals.

### Ethical Considerations

#### Ethical Approval

The BM-MA is a digital nonpharmaceutical mental health intervention whose content was adapted from 1 of the existing mindfulness-based apps that has been shown to be safe for treating anxiety [41]. The trial protocol was approved by the Research Ethics Committee at Universitas Pendidikan Ganesha (1828/UN48.16/LT/2022) and publicly registered (Chinese Clinical Trial Registry with protocol number ChiCTR2300068085). The intervention also ensured that no participant will be stigmatized for their participation. An introduction meeting was held on Zoom to address the potential stigma around mental health interventions and explore strategies for effectively managing this stigma. We will be communicating to the research committee in the case of any important protocol modifications. Written informed consent was obtained from each participant. The intervention content, which includes an activity to learn and practice mindfulness exercises via a mobile app, was rewritten or sensitive or potentially objectionable terms were eliminated.

#### Data Management

Data collection was conducted electronically. The data were securely stored on password-protected computers, and only members of the study group have access to them. To ensure the confidentiality of the participants, distinct, unique study numbers were used for data storage, tracking, and reporting. An encryption protocol used complex algorithms to obscure data, which it then decoded using an encryption key that the interaction’s sender provided. The data cleaning procedure systematically and proactively identified mistakes. Errors were deliberately and methodically sought out through the data cleaning procedure. Repeated imputation was used to manage missing data due to its reliability in dealing with missing data in a feasibility study and its availability for the vast majority of data types [42].

### Data Analyses

The sociodemographic characteristics of the participants (eg, age) will be analyzed descriptively. Missing data, including participants who dropped out, will be treated using the intention-to-treat principle with multiple imputations of missing values [42]. Intention-to-treat analysis is a statistical method used in prospective randomized studies. It involves including all individuals who were randomly assigned to a group, regardless of whether they received any sort of treatment. These participants are then examined on the basis of their initial group assignment. This methodology enables the researcher to derive precise and impartial judgments regarding the efficacy of an intervention. This approach maintains the advantages of randomization, which cannot be presumed when using alternative methods of analysis.

The data will be examined using repeated-measures ANOVA with groups (BM-MA vs control) and 3 time periods as factors (baseline, day 21, day 41). In addition, Pearson correlation analysis will be undertaken to determine whether the subjective ratings of involvement and experience with the BM-MA by participants correlate with any potential improvements in well-being experienced by the BM-MA group. The variation in findings between the 2 groups will be encompassed by the 95% CI range for the significance of the effect. The amount of effect (Cohen d) will be calculated by dividing the median variation (from baseline, monitoring, and end line to follow-up) obtained from the results of the linear mixed model by the pooled SD at baseline.

Transcription will be conducted for all records of structured qualitative interviews. The qualitative data will undergo deductive theme analysis using a framework and will be used to create an initial codebook. The qualitative data will be analyzed using an iterative method by 2 coders, who will independently code all transcripts and then discuss any inconsistencies until consensus is established. The resulting comprehensive codebook will be input into qualitative analysis software.

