### Study Objectives

This feasibility study will evaluate the possible adoption of the BM-MA in real-world contexts. The secondary objectives are to determine the effectiveness of BM interventions based on mobile apps in enhancing life satisfaction, self-compassion, and a sense of self-efficacy and in reducing participant-reported anxiety and stress symptoms. The following scientific questions will be addressed:

Can the BM-MA be accepted into the community practice of Indonesian senior high school teachers to enable scale-up?Throughout the study, could the BM-MA be applied as intended?Could the BM-MA implementation be continued throughout the conclusion of the research?Does the BM-MA reduce stress and promote life satisfaction, self-compassion, and a sense of self-efficacy, as stated by participants?Does the BM-MA reduce participant-reported anxiety symptoms?

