### Acceptability and Feasibility

A mixed methodological study was used to evaluate the BM-MA’s feasibility and acceptability. Acceptability is defined as the extent to which an app is suitable [28], and is assessed by analyzing participants’ qualitative responses to structured interviews. The quantitative scale used to measure feasibility was the Client Satisfaction Questionnaire-8 (CSQ-8) [28]. Each item in the CSQ-8 is rated on a scale of 1-4, and total scores range from 8 to 32. More than 70% of participants must receive a score of 24 or above on the CSQ-8 [28], given a 10% acceptable error rate [29], and participate in structured qualitative interviews for acceptance to be determined.

Feasibility is defined by Feeley et al [30] as the ease of deployment of an app among adults. In this study, on the basis of app scores, feasibility will be evaluated descriptively by examining the ease of recruitment, enrollment rate, and attrition rate. Participants will also be required to complete an in-person final evaluation. End-of-line evaluations will involve the viability and acceptance of the mobile app, as well as structures qualitative interviews.

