### Randomization and Blinding

Participants from 2 public senior high schools were randomly assigned to the BM-MA group or the CG in a 1:1 ratio. The app arbitrarily selected a block size (2, 4, or 6) and assigned a random order within the block. For example, we randomly allocated 30 participants to each group in this scenario. The BM-MA group was denoted as “M” and the CG as “C.” The possible groupings were MCCM, MMCMCC, CM, MC, and CMCM. As part of the screening consent procedure, participants were informed that this will be an interventional study in which they might be randomized to a variety of BM-MA groups.

The prior online mindfulness intervention revealed a substantial potential for attrition. To proactively address this problem, we identified all potential avenues for recruiting and factored in the attrition rate when determining the appropriate sample size [27,30]. Considering the features and design of this pilot project, it would not be possible to blind the treatment assignment and result evaluation. However, participants were provided with information regarding the significance of a 2-arm study design following the CONSORT checklist (can be seen in Multimedia Appendix 1) and were strongly advised against disclosing their group allocation to their coworkers. Although there may be possible problems, this strong methodology will guarantee that the BM-MA intervention is carried out with a high level of academic excellence.

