#### Measurement of Primary Outcome

The evaluation of the BM-MA implementation in real-world contexts will be the primary outcome for this study. This study will evaluate the adoption of the BM-MA with an engagement and experience questionnaire. On the basis of Howell et al’s [22] findings, a questionnaire will be designed to allow participants to rate their experience using the app.

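### The blanket multiple-imputation rule exempts no outcome, so app ratings that are the primary adoption measure would be imputed for teachers who left, which risks overstating adoption

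*Protocol article*

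**What the plan says.** All references are to the protocol article.

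- **Missing data.** Data Analyses gives one rule: "Missing data, including participants who dropped out, will be treated using the intention-to-treat principle with multiple imputations of missing values". Data Management gives it again: "Repeated imputation was used to manage missing data due to its reliability in dealing with missing data in a feasibility study". It adds that the method suits most kinds of data. Neither section exempts an outcome.
- **Primary outcome.** Measurement of Primary Outcome says: "The evaluation of the BM-MA implementation in real-world contexts will be the primary outcome for this study". It then names the instrument: "This study will evaluate the adoption of the BM-MA with an engagement and experience questionnaire". Table 1 schedules engagement and experience questionnaires at baseline, day 21 and day 41.
- **Second use of the ratings.** Data Analyses also plans a Pearson correlation, in the BM-MA group, between these ratings and improvement in well-being.
- **Study questions.** Study Objectives asks about community uptake, about use as intended, and about continuation: "Could the BM-MA implementation be continued throughout the conclusion of the research".
- **Dropout.** Randomization and Blinding warns: "The prior online mindfulness intervention revealed a substantial potential for attrition". No rate is given. Acceptability and Feasibility adds that "feasibility will be evaluated descriptively by examining the ease of recruitment, enrollment rate, and attrition rate".

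**The concern.** Multiple imputation makes sense for a quantity that exists but was not observed. A teacher who drops out still has an anxiety level on day 21, so a missing GAD-7 score is a proper target. An app rating is different. A teacher who never opened the app has no experience to rate, and for one who stopped and left, the leaving may be the answer to the adoption question. Imputation would give both a plausible rating learned from teachers who stayed.

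At stake is the primary result. If teachers leave because they did not take to the app, the imputed ratings move the adoption summary towards the stayers, and the shift grows with dropout. The same imputed ratings would enter the planned correlation with improvement, and part of that association would then come from the imputation model.

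**Working it through.** **Inputs from the article.** There are 30 teachers in the BM-MA arm (Recruitment and Sample Size). Attrition is described as potentially substantial, with no rate. The imputation model is not described. The figure of 30 per arm comes with no numeric effect size, power or dropout rate, so it cannot be reproduced, and this point does not depend on it.

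**Assumed inputs.** Adoption is summarised as a share of teachers with a favourable rating; the article defines no such share. Let p be that share among stayers (80%), d the dropout (10% to 40%) and a the true share of adopters among leavers.

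**Formulas.**
- Imputation with no informative predictors gives leavers the stayers' share, so the reported figure is (1 − d)·p + d·p = p.
- The true figure is (1 − d)·p + d·a.
- Overstatement = d·(p − a). It is largest at a = 0, where it equals p·d, and zero at a = p.

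**Results with p = 80%.**

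| Dropout d | Stayers of 30 | Imputed | a = 0 | Gap (points) | a = 40% | Gap (points) |
|---|---|---|---|---|---|---|
| 10% | 27 | 80% | 72% | 8 | 76% | 4 |
| 20% | 24 | 80% | 64% | 16 | 72% | 8 |
| 30% | 21 | 80% | 56% | 24 | 68% | 12 |
| 40% | 18 | 80% | 48% | 32 | 64% | 16 |

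Example: at d = 20% and a = 0, 0.80 × 24/30 = 0.64, and 0.80 − 0.64 = 0.16 = 0.80 × 0.20. With p = 70% the a = 0 gaps at 10% and 20% dropout are 7 and 14 points; with p = 90% they are 9 and 18.

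**Does better imputation remove the gap?** This was simulated with 30 teachers, an assumed rating with true mean 3.00 and SD 0.6, and a usage measure correlated 0.6 with the rating and included in the imputation model. Missingness was 30% to 33%.

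| Why teachers leave | Mean in completers | Mean after imputation |
|---|---|---|
| Unrelated to rating | 3.00 | 3.00 |
| Depends on usage only | 3.10 | 3.00 |
| Depends on the rating itself | 3.17 | 3.11 |

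The bias is therefore conditional. It is absent in the first two cases. In the third, imputation removes only part of it, even with usage in the model.

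**The case against.** The strongest reply is that the rule was never meant for the adoption ratings. After stating it, Data Analyses explains intention-to-treat in terms of group assignment and judging efficacy, then turns to the repeated-measures ANOVA. The abstract also places intention-to-treat directly after that ANOVA. Attrition is to be reported descriptively as a feasibility result, so dropout would not be hidden. Handling of missing data outcome by outcome is often left to a fuller plan.

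This narrows the harm but does not remove it. Data Management repeats the rule on feasibility grounds and for most kinds of data, which reaches beyond the symptom scales. The ratings also belong to the quantitative analysis through the correlation. A separately reported attrition rate does not correct an adoption figure that contains imputed ratings. The point is about a rule the article states, not about one it omits.

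Three stronger readings are tempting, and the article does not support them.

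- **That adoption is overstated, as a fact.** This needs the rule to be applied to the ratings, and dropout to depend on poor adoption beyond what the imputation model holds. Neither is established. A teacher lost after day 21 may already have an end-line rating, and leaving the study is not the same as abandoning the app.
- **That the corrected figure would fail a 70% criterion.** The article says "More than 70% of participants must receive a score of 24 or above on the CSQ-8". That threshold belongs to the CSQ-8 and to acceptability. The engagement questionnaire has no stated threshold.
- **That app logs can settle who adopted.** The Intervention section says the app lets participants track their practice. It does not say the study team receives those records.

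**Conclusion.** The point holds as a risk created by the wording. The stated rule covers the primary adoption ratings and the ratings in the correlation, and it suits neither, because for some leavers there is no experience to impute and their leaving bears on the study questions.

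The size cannot be determined from the article. The illustrative 8 points (10% dropout) and 16 points (20% dropout) rest on an assumed 80% favourable share among stayers, assumed dropout rates and an imputation model with no informative predictors. They also treat every leaver as a true non-adopter, so they are upper bounds. The point concerns how adoption is scored. It does not question imputation for the between-group comparison of psychological outcomes.

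**What to change.** In Data Analyses:

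1. Limit multiple imputation to the psychological scales: GAD-7, GHQ-12, PSS, SLS, SCS-SF, TSES and FFMQ. Align the sentence in Data Management.
2. Do not impute engagement and experience ratings, either for the primary outcome or for the Pearson correlation.
3. Report observed ratings with the number of raters out of all 30 randomised BM-MA teachers.
4. Give adoption over all 30, counting leavers without a rating as non-adopters, beside the figure among observed raters. The two together show how far the conclusion depends on the leavers.
5. Use app usage logs to classify leavers only if the team holds them.

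**Cost.** Analysis and wording only; no new data are needed. The Results section says that analysis has been done and the paper is being written, so the change can be made in the report and declared as a departure from the published plan. The downside is a lower adoption figure, and some leavers who did use the app may be counted as non-adopters.

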**Methods:**

We followed the SPIRIT (Standard Protocol Items: Recommendations for Interventional Trials) 2013 statement for this feasibility randomized controlled trial (RCT) protocol. A total of 60 Indonesian senior high school teachers were recruited for this study and randomly assigned to either the intervention group (BM-MA) or a wait-list control group (CG) in a 1:1 ratio. The BM-MA group was required to engage in mindfulness practices using the app for 10-20 minutes per day for 3 weeks. All participants were assessed with a battery of self-report measures at baseline, postintervention, and at 1-month follow-up. Validated scales used to measure the outcome variables of interest included the Satisfaction With Life Scale (SLS), the Teachers’ Sense of Efficacy Scale (TSES), the Self-Compassion Scale—Short Form (SCS-SF), Generalized Anxiety Disorder-7 (GAD-7), General Health Questionnaire-12 (GHQ-12), and the Five Facet Mindfulness Questionnaire (FFMQ). The practicality and acceptability of the app will be evaluated using the Client Satisfaction Questionnaire-8 (CSQ-8) and structured qualitative interviews. Data from the interviews will be analyzed with the deductive thematic analysis framework as a process of qualitative inquiry. Repeated measures ANOVA with groups (intervention vs control) as a between-subject factor and time as a within-subject factor (baseline, postintervention, and 1-month follow-up) will be used to examine the effects of the BM-MA on the outcome variables. The data will be analyzed using an intent-to-treat approach and published in accordance with CONSORT (Consolidated Standards of Reporting Trials) recommendations.

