### Recruitment and Sample Size

This study’s sample comprised Indonesian high school teachers. The sample was drawn from 2 public senior high schools after a request for volunteers was sent over email by local government partners. Individuals who answered within 1 week were directed to a webpage on Qualtrics that describes the study and screening process. In addition, recruiting advertisements based on the opinion of the school principals were distributed via the schools’ social media. Individuals who passed the screening process were included in the participant pool.

The inclusion criteria for the feasibility study were Indonesian certified senior high school teachers (1) who are aged 18 years and older, (2) can read and write in Indonesian, (3) have access to a smartphone, and (3) have a total Generalized Anxiety Disorder-7 (GAD-7) score of no more than 14 and a total General Health Questionnaire-12 (GHQ-12) score of no more than 20. The exclusion criteria for the feasibility study were (1) regular practice of mindfulness meditation (eg, 15-20 minutes per day, 2-3 times per week), (2) a history of ongoing and present treatment for a mental disorder, (3) a positive response to GHQ-12 questions regarding suicidal ideation, and (4) refusal to provide written informed consent. These criteria were designated to recruit participants without prior regular experience in mindfulness practice and with no severe symptoms of depression and anxiety. The criteria also contributed to a more homogenous selection of participants across conditions.

Random sampling was used in the 2 public senior high schools in Indonesia, with the unit that was randomized being the senior high schools themselves. The sample size for this feasibility study was 30 participants for each study arm, with 95% CIs and small standardized effect sizes [27].

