### Assessments Tools

There were 4 points of measurement: screening, baseline, end line, and follow-up. In Table 1, following the SPIRIT 2013 statement [26], an overview of the evaluation instruments used in this study is presented. Both groups received compensation for the time they spent and the internet data they used throughout the baseline, end line, and follow-up periods. The compensation amounts were ~US $3 for baseline, US $7 for the end line, and US$ 10 for follow-up, which is equivalent to the average cost of obtaining internet data in Indonesia. The act of providing monetary compensation as reimbursement is noncontroversial and commonly acknowledged [31].

**Table 1 table1:** Study outcomes and time points of measurement.

Outcome	Instrument	Screening	Baseline	End line	Follow-up
			Day 1	Day 21	Day 41
Sociodemographics (age, education level, sex, marital status, occupation, years as schoolteacher, salary, schoolteacher status)	Demographics	Y^a^	Y	—^b^	—
Source of obtaining BM-MA^c^ information	Demographics	Y	—	—	—
Mental health care service history	Demographics	Y	Y	Y	Y
Smartphone ownership	Demographics	Y	Y	—	—
Internet access	Demographics	Y	Y	—	—
Contact details	Demographics	Y	—	—	—
Convenient contact times	Demographics	Y	—	—	—
Perceived stress	PSS^d^	—	Y	Y	Y
Depression symptoms	GHQ-12^e^	Y	Y	Y	Y
Anxiety symptoms	GAD-7^f^	Y	Y	Y	Y
Well-being	SLS^g^ and SCS-SF^h^	—	Y	Y	Y
Self-efficacy	TSES^i^	—	Y	Y	Y
Mindfulness trait	FFMQ^j^	—	Y	Y	Y
Engagement and experiences with the BM-MA	Questionnaires	—	Y	Y	Y
Qualitative interview of feasibility and acceptability	Interview guideline	—	—	Y	Y

^a^Y: measured.

^b^Not measured.

^c^BM-MA: brief mindfulness–based mobile app.

^d^PSS: Perceived Stress Scale.

^e^GHQ-12: General Health Questionnaire-12.

^f^GAD-7: Generalized Anxiety Disorder.

^g^SLS: Satisfaction With Life Scale.

^h^SCS-SF: Self-Compassion Scale—Short Form.

^i^TSES: Teachers’ Sense of Efficacy Scale.

^j^FFMQ: Five Facet Mindfulness Questionnaire.

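### Cohen d is defined through a median change from a linear mixed model that is not the planned analysis, so it cannot be computed reproducibly; separately, treating baseline as a time level costs precision

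*Protocol article*

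**What the plan says.** The abstract's Methods paragraph and the Data Analyses section agree on the test. The abstract has "Repeated measures ANOVA with groups (intervention vs control) as a between-subject factor and time as a within-subject factor", and its time levels include baseline: "time as a within-subject factor (baseline, postintervention, and 1-month follow-up) will be used to examine the effects of the BM-MA". Data Analyses repeats it: "The data will be examined using repeated-measures ANOVA with groups (BM-MA vs control) and 3 time periods as factors", the three periods being baseline, day 21 and day 41. Neither place names a baseline covariate or says which ANOVA term is the treatment test.

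Later in the same paragraph of Data Analyses, Cohen d is to be calculated by "dividing the median variation (from baseline, monitoring, and end line to follow-up) obtained from the results of the linear mixed model". The divisor is the SD of the baseline scores, pooled over the arms. This is the article's only mention of a linear mixed model.

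On timing, the assessments section says "There were 4 points of measurement: screening, baseline, end line, and follow-up", and Table 1 shows the same four columns.

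**The concern.** An effect size should be the standardised form of the contrast that the analysis estimates. Here the test comes from one model and the effect size from another that is not described. The numerator is a statistic that this second model does not produce, and the interval it covers refers to a time at which nothing is measured. The sentence also does not say whether the change is within or between arms. Two competent analysts could follow it and report different values of d.

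The Discussion says the findings will decide whether the app is recommended for efficacy testing, and the Conclusion ties future use to a considerable positive effect. The size of the effect therefore matters to how the trial is read. By the article's own account, data analysis ran from March through May 2024, so an unsettled definition leaves room to settle it after the results are known.

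The second question is efficiency. With 30 teachers per arm, an analysis that makes poor use of the baseline scores already collected loses precision that could be had at no extra burden.

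**Working it through.** **1. Is there a stated figure to reproduce?** No. The only design figure is the sample size: "The sample size for this feasibility study was 30 participants for each study arm, with 95% CIs and small standardized effect sizes". No power, SD, numerical effect size or correlation is given, and no value of d is reported. What follows therefore tests the definition and the precision, not a published number.

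**2. The effect-size sentence against the rest of the article.**

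| Element of d | Effect-size sentence | Elsewhere in the article |
|---|---|---|
| Model | linear mixed model | repeated-measures ANOVA (abstract; Data Analyses) |
| Statistic | median | a linear mixed model gives mean differences; Cohen d is a mean difference over an SD |
| Times | baseline, monitoring, end line, follow-up | screening, baseline, end line, follow-up |
| Contrast | not stated | the preceding sentence speaks of differences between the two groups |
| Denominator | pooled baseline SD | clear and usable |

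Only the denominator can be carried out as written.

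**3. How much could the median matter?** This depends on the shape of the changes, which is unknown.
- Normal changes with mean −0.50 SD: median −0.50, mean −0.50, no difference.
- An illustrative skewed case with 40% responders: d is −0.48 by median and −0.53 by mean, a gap of 0.05. For scale, the unadjusted 95% CI half-width for d at 30 per arm is about 1.96 × √(2/30) = 0.51.
- A constructed extreme, in which 45% improve by exactly 1 SD and 55% do not change: the median is 0 and the mean is 0.45 × 1 = 0.45 SD.

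The discrepancy can be anything from nil to large.

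**4. Cost of keeping baseline as a time level.** Assume equal variances (SD 1) and a baseline-to-follow-up correlation rho. Rho is not in the article, so a range is shown. For one follow-up, the variance per participant is:
- group-by-time contrast (change from baseline): 2(1 − rho)
- baseline as covariate: 1 − rho²
- ratio: 2(1 − rho)/[(1 − rho)(1 + rho)] = 2/(1 + rho)

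Power below is two-sided at 0.05, for 30 per arm and an assumed effect of 0.5 SD, by normal approximation. Effective n is 30 divided by the ratio.

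| rho | Change | Adjusted | Ratio | SE increase | Effective n per arm | Power, change | Power, adjusted |
|---|---|---|---|---|---|---|---|
| 0.3 | 1.40 | 0.91 | 1.54 | 24% | 19.5 | 37% | 53% |
| 0.5 | 1.00 | 0.75 | 1.33 | 15% | 22.5 | 49% | 61% |
| 0.7 | 0.60 | 0.51 | 1.18 | 8% | 25.5 | 71% | 77% |
| 0.8 | 0.40 | 0.36 | 1.11 | 5% | 27.0 | 87% | 90% |

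**5. Separating adjustment from averaging.** At rho 0.5, with an effect of 0.5 SD at both post-baseline times and compound symmetry, power is about 49% for the 2-df interaction. It is 59% for the change averaged over both follow-ups, 60% for baseline-adjusted Day 21, and 77% for the baseline-adjusted average. Only part of the distance from 49% to 77% comes from baseline adjustment; the rest comes from averaging two times in a 1-df contrast.

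**The case against.** The strongest defence is that *median* is loose wording. The quantity is taken from a mixed model and divided by a pooled SD, which points to an ordinary model-based mean change, and in that case nothing would be numerically wrong. The preceding sentence also makes a between-group reading available, and a condensed article may leave the mixed-model specification to a fuller document. This stands as a limit on size. It does not remove the contradiction: the article itself names one analysis, draws its effect size from another, and lists a time that its own schedule lacks.

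A second defence is that a group-by-time ANOVA with baseline as a level is valid in a randomised trial, and that both places describing it agree. That also stands. The contrast is unbiased, and the loss is of precision only, becoming small when rho is high.

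Three stronger readings might be inferred, and the document supports none of them.
- That a reported Cohen d is wrong. The article reports none.
- That the treatment effect is diluted to two thirds. This would follow only if the group main effect over all three times were read as the treatment effect, since (0 + d + d)/3 = 0.67d. The article never says so, and the interaction is the conventional term.
- That baseline adjustment alone would bring power into the region of 77%. As the working shows, part of that gain comes from averaging.

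Nor does the article say that d will be used to size a later trial.

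**Conclusion.** The concern holds in two limited parts, and together they should be fixed.

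First, the effect-size rule contradicts the planned analysis and the measurement schedule, and it names a statistic that its own model does not estimate. This follows from the text alone. The numerical consequence is unknown and may be nil if changes are symmetric.

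Second, the ANOVA as written gives up precision. For one follow-up the variance is 54% larger than with baseline adjustment at rho 0.3 and 11% larger at rho 0.8. This rests on an assumed rho and on equal variances over time. The loss belongs to the ANOVA as specified: a mixed model that keeps baseline as an outcome but constrains the arms to a common baseline mean would not suffer it.

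The article's primary outcome is implementation of the app, and the affected outcomes are secondary in a 60-person feasibility trial. That keeps the severity moderate.

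**What to change.** Replace the ANOVA sentence and the effect-size sentence with one model for the secondary outcomes:
- **Model:** a linear mixed model with the Day 21 and follow-up scores as outcomes; arm, time, arm-by-time and baseline score as terms; and a stated within-person covariance. Fit it to the multiply imputed data already planned.
- **Estimate:** the adjusted between-arm mean difference with its 95% CI at each of the two times.
- **Effect size:** that difference divided by the pooled baseline SD, at a named time.
- **Wording:** delete *median* and *monitoring*, and align the abstract.
- **Disclosure:** state in the results paper that the definition was changed after data collection.

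The cost is small. No new data are needed, but a covariance structure has to be chosen and the existing data re-analysed.
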